#### Maternal urine

Participants were provided with detailed instructions on how to collect the proper sample. Mid-stream clean catch urine samples were obtained from the participants at the study health centre using sterile urine collection cups. The collected samples were then transferred into 10 mL boric acid vacutainers for transport until urine culture was processed at APHI for the main study. The samples were aliquoted into 5 mL sterile cryotubes for storage at APHI for future analysis. Additionally, UTI testing was done with urine culture, and antibiotic susceptibility testing was conducted using Vitek cards.

#### Maternal vaginal swab

Participants were instructed by the health centre laboratory technicians and study nurses on how to self-collect mid-vaginal swab samples. Formative work was conducted prior to the study regarding the self-collection of swabs, and it was both highly acceptable (96%) and high-quality. Based on this formative work, sample collection instructions were revised to improve quality. Following handwashing with soap, women used nylon swabs to swab their vagina and placed them on a specimen collection tray. Two swabs were collected. STIs were detected using self-collected vaginal swabs tested for gonorrhoea and chlamydia with the GeneXpert platform. The laboratory technicians then transferred the remaining swabs into the DNA/RNA shield collection tubes, securely capped them and gently inverted the tubes several times (ensuring no foaming). Samples were transported to the APHI and aliquoted into sterile cryotubes and stored at −80°C.

#### Maternal blood

##### Serum

Trained laboratory technicians performed venipuncture to collect a total of 7 mL of whole blood from participants during each visit. The blood was drawn into a yellow-top serum separator tube (SST) and kept upright at room temperature until transport to APHI. On arrival at APHI, the SST tube was centrifuged at varying speeds (5, 10 or 15 000 RPM) to separate the serum from the sediment layers. The top serum layer was then carefully aliquoted in up to two sterile cryovials using a micro-pipette and stored at −80°C.

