## Methods

### Study setting and population

The ENAT study was conducted in 12 health centres in Amhara, Ethiopia. For ENAT, pregnant women at ≤24 weeks gestation presenting for antenatal care at the study sites were enrolled in the study if they met the eligibility criteria. Women were excluded if they had a non-viable pregnancy at ≤24 weeks gestation, determined by a lack of heartbeat on the enrolment ultrasound or were unable to return for follow-up visits (typically >2 hours travel distance from health centre). Within the ENAT study, the biospecimen substudy was conducted in a subset of six health centres (three enhanced nutrition and three routine care centres) that had functional laboratory rooms and were accessible from the regional city/central laboratory (Ambesamie, Arbgebeya, Lalibela, Legdiya, Yifag and Yismala). The LIDG study enrolled the infants born to women included in these ENAT biospecimen health centres who intended to stay in the study catchment area after giving birth. Children with major congenital anomalies, severe morbidity or developmental disorders, acute symptoms of illness (eg, headache, vomiting or dizziness) or neonatal encephalopathy were excluded from the study.

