### Study design

The ENAT study was a pragmatic, open-label 2×2 factorial, randomised clinical effectiveness study with cluster-randomisation of an enhanced nutrition package (ENP) intervention and individual-level randomisation of an enhanced infection management package (EIMP) intervention (figure 1). The detailed study protocol has been previously published^11^ and this protocol paper details the protocols for biospecimen collection and planned analysis.

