### Biospecimen collection and processing

Maternal whole blood, serum, stool, urine, vaginal swabs and breastmilk samples were collected at trimesters 1, 2 and 3, and 1–3 months postdelivery. Umbilical cord whole blood and serum, and infant whole blood and stool were also collected at birth and 1–2 months postnatal visit(s), respectively. For samples collected during the COVID-19 pandemic, all local health and prevention protocols and guidance were followed to collect and process biospecimens. Specimens were collected at each study health centre by trained laboratory technicians assisted by study nurses and transported using triple packaging containing ice packs within 48 hours of collection to the Amhara Public Health Institute (APHI) central laboratory for processing and longer storage at −80°C. A comprehensive list and timing of biospecimens collected in this study are shown in table 2.

**Table 2 T2:** ENAT study visits and biospecimen collection

Biospecimen type (collection mechanisms)	Enrolment visit (<24 week)	ANC follow-up visit (~30–34 weeks)	Birth (within 72 hours of birth)	Postnatal follow-up visit (1–6 months)*
Urine	M	M		
Vaginal swab	M	M		
Serum	M	M	C	
Whole blood (DBS)	M	M	C	I
Whole blood (VAMS)	M	M	C	I
Stool (Genotek)	M	M		M, I
Stool (TaqMan)	M	M		M, I
Breastmilk				M

* Postnatal visits were stopped prematurely due to conflict in the study region.

ANC, antenatal care; C, cord; DBS, dried blood spot; ENAT, Enhancing Nutrition and Antenatal Infection Treatment; I, infant; M, maternal; VAMS, volumetric absorptive microsampling.

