#### Intervention effects

In our primary analysis, we will examine differences in biomarkers or ’omics profiles across the randomised intervention study arms. We will use intention-to-treat as the primary analyses where individuals are analysed according to their originally assigned study arm, and in secondary analysis, we will also explore effects of individual interventions (ie, BEP) and adherence/dose. Outcomes will be compared between the primary factors (ENP or EIMP) to determine their marginal effects (ENP vs not-ENP, and EIMP vs not-EIMP). We will estimate differences in biomarkers, using linear mixed regression models. Potential confounding bias should be minimised due to the randomised study design; however, we will assess group differences in demographic and clinical characteristics at both cluster- and individual randomisation levels, as recommended by Consolidated Standards of Reporting Trials.^28^ Baseline covariate imbalances associated with both the outcome and exposure status (p<0.10) will be included in adjusted models as potential confounders. Multiple births will be excluded from analyses using birth outcomes due to the known increased rate of preterm birth and growth restriction among multiple deliveries. When large volumes of tests are conducted for metabolomics or genomics analyses, we will use the Benjamini-Hochberg method to correct for multiple testing, as appropriate.

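### Time to centrifugation of the serum for the iron markers lies outside the stated covariate rule and could be confounded with the centre-assigned nutrition contrast; any bias is of unknown size and may be nil

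*Protocol article*

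**What the plan says.** Under Maternal blood, Serum, the article says that the blood was drawn into a serum separator tube and "kept upright at room temperature until transport to APHI". Only after arrival there, "the SST tube was centrifuged at varying speeds (5, 10 or 15 000 RPM) to separate the serum from the sediment layers". No rule says which speed applied to which tube.

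Under Biospecimen collection and processing, specimens of all types were "transported using triple packaging containing ice packs within 48 hours of collection". Table 2 lists maternal serum at enrolment and again at the antenatal follow-up visit.

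Study design describes "cluster-randomisation of an enhanced nutrition package (ENP) intervention and individual-level randomisation of an enhanced infection management package (EIMP) intervention". Study setting and population says that the substudy used six of the twelve centres, three per nutrition arm, which had working laboratory rooms and "were accessible from the regional city/central laboratory".

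Iron status makes ferritin, sTfR and hepcidin serum outcomes, with total body iron to be calculated. Statistical analyses makes the comparison of biomarkers between arms the primary analysis. Under Intervention effects, the imbalance check covers demographic and clinical characteristics, and the adjustment rule reads: "Baseline covariate imbalances associated with both the outcome and exposure status (p<0.10) will be included in adjusted models as potential confounders".

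The strengths and limitations box admits delayed freezing and differences in day or time of collection. It does not mention delay to centrifugation or spin speed.

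**The concern.** The article describes a source of measurement variation in primary-analysis outcomes and fixes a covariate rule that does not reach it. Hours from collection to centrifugation of the follow-up tube is neither a baseline variable nor a demographic or clinical one.

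This matters more here than in an individually randomised trial. If time to centrifugation differs between centres, it differs between units that each carry a single nutrition arm, and three centres per arm give randomisation little room to balance it. If an iron marker shifts while the serum stays on the clot, part of an ENP difference could be a difference in handling. The safeguards stated elsewhere do not cover this: internal controls are for metabolomics batch effects, and the 10% retest is for urinary iodine. Neither would show a shift that arose in the serum tube before it was spun.

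**Working it through.** The plan gives no figure on this point, so there is nothing to reproduce. What follows sets the statements together and shows what range of effect they leave open.

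**Inputs from the documents:** six centres, three per nutrition arm; 532 dyads; transport up to 48 h after collection; covariate rule at p<0.10; serum at enrolment and at follow-up.

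**Assumptions (not in the documents):** drift of 0 to 1% per hour on the clot; difference in mean delay between arms of 0 to 24 h; log-scale SD of 0.7; 266 women per arm (532/2); slope of follow-up on enrolment value of 0.3 to 0.7.

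**1. How unequal can three against three be?** There are C(6,3) = 20 splits. The three centres with the longest delay share an arm in 2 of 20, or 10%. If centre delays were equally spaced over 0 to 48 h, the absolute arm difference in mean delay would average 12.2 h, with a maximum of 28.8 h. These figures scale with the spread: over 0 to 12 h, the average is 12.2 × 12/48 = 3.0 h and the maximum 7.2 h.

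**2. What would that do to a marker?** False difference in SD = ln(1 + rate) × hours / 0.7.
- zero drift or zero delay difference: 0
- 0.5%/h, 6 h: 0.00499 × 6 / 0.7 = 0.04
- 0.5%/h, 12 h: 0.00499 × 12 / 0.7 = 0.09
- 1%/h, 12 h: 0.00995 × 12 / 0.7 = 0.17
- 1%/h, 24 h: 0.00995 × 24 / 0.7 = 0.34

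The last line combines the upper ends of both assumptions.

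**3. What would a fixed offset do to a test?** With 266 per arm and an analysis of individuals that ignores centre, an offset of 0.1, 0.2 or 0.3 SD gives p<0.05 in 21%, 64% or 93% of trials. The article plans mixed models, so this shows the size of the hazard and does not describe the planned analysis.

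**4. Would a p<0.10 screen find a centre-level imbalance?** An exact test on six centres has a smallest two-sided p of 2/20 = 0.10, so it can never fall below 0.10. A t-test on centre means (4 df) flags an imbalance of 1 centre-level SD in 27% of cases and of 2 SD in 65%. The rule would therefore be unreliable even if handling were added to the list it screens.

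**5. Can the enrolment marker stand in?** Enrolment serum came from the same centres by the same route, so a stable centre artefact would be in it too. In an individual-level screen, offsets of 0.1, 0.2 and 0.3 SD would be flagged at p<0.10 in 31%, 75% and 97% of cases. Once the marker is in the model, the share of a stable offset left is 1 − slope, which is 70% at a slope of 0.3 and 30% at 0.7. An offset of 0.2 SD would shrink to between 0.14 and 0.06 SD. A change in transport timing between the two visits would not be captured.

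**6. Spin speed and the infection package.** Speed was set at the central laboratory, and nothing ties it to centre or arm. The infection package is randomised individually, so its contrast is made largely among women whose tubes came from the same centre.

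**The case against.** The strongest reply has five parts.

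- **Silence is not prohibition.** A condensed article may leave technical covariates to an analysis plan that is not shown, and the stated rule does not say that nothing else may enter. This stands as far as omission goes. What remains is that the one rule that is stated suits neither a centre-level contrast nor a variable that arises after baseline.
- **No delay difference is documented.** The 48 h is an upper limit for all specimen types, transit was on ice packs, and the centres were chosen partly for access to the laboratory. All of this stands. So does the point that no instability of ferritin, sTfR or hepcidin is stated.
- **Adjustment is possible in part.** If the enrolment marker is screened as a clinical baseline variable, the existing rule may bring it in. This stands, subject to the residue in step 5.
- **A correct cluster analysis holds its error rate.** If delay is unrelated to arm, centre-level handling variance with an assumed intraclass correlation of 0.01, 0.02 or 0.05 gives type I error of 15%, 24% or 40% when centres are ignored. A centre-level t-test keeps it at about 5%. This stands, but it concerns the error rate over repeated allocation. It does not make the estimate from this particular set of six centres free of a handling difference.
- **A delay covariate has little to work with.** With six centres, a delay that follows the centre is nearly collinear with it. This stands and limits the remedy.

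A reader might infer more: that distance to the laboratory produces an apparent nutrition effect, that the three speeds add to it, and that the plan is unable to adjust for it. The documents support none of these steps. They give no distances or transit times, they place centrifugation at the central laboratory, and they provide enrolment serum that would carry a stable artefact.

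**Conclusion.** The concern holds in limited form. Known variation in handling of the serum for primary-analysis iron outcomes is not named in the stated adjustment rule and is not reliably captured by it. Because ENP is assigned by centre, three against three, a difference in delay between centres could be confounded with the ENP contrast. Spin speed is unstandardised variation that may add noise, and the infection contrast is largely protected.

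The size cannot be determined from the documents. Under the assumed ranges it runs from nil to 0.34 SD, with 0.09 to 0.17 SD at a 12 h difference, and it is exactly nil if the markers are stable or if the arms have equal delay. This justifies an inexpensive safeguard. It does not justify a claim that the ENP result on iron status is biased.

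**What to change.** Table 3 still gives the laboratory for the serum iron assays as undecided, so there may be time to settle this before results exist.

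- Where they were recorded, prespecify hours from collection to centrifugation and centrifuge setting (three levels) as technical covariates for every serum analyte, entered regardless of the p<0.10 rule.
- Adjust each follow-up marker for its enrolment value, also outside that rule.
- Tabulate delay and setting by centre and by nutrition arm.
- Repeat the ENP contrast in samples with shorter delays, with the cut-off fixed before any comparison by arm.
- If delays in the two arms barely overlap, or were not recorded, state that the ENP effect on iron markers cannot be separated from handling, and add serum handling to the listed limitations.

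The cost is plan wording and linking collection and spin records to aliquots. The documents do not say that these times or settings were logged tube by tube, so the linking may prove impossible for some samples. A delay term will be weakly identified between six centres and may widen the ENP interval, and the sensitivity sample will be smaller.

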##### Dried blood spots (DBS)

Maternal prenatal DBS samples were collected from women while they were providing blood for routine laboratory testing (haemoglobin/HIV/syphilis) in trimester 1. Samples from trimesters 2 and 3 were collected via finger-stick. After the blood was collected into EDTA tubes, the tubes were gently inverted 8–10 times. Using a micropipette, 50–80 µL of blood was placed on a single spot on a Whatman 903 Proteinsaver Card (Cytiva, US), and this process was repeated three more times for a total of four spots. The Whatman cards were air-dried for 24 hours at the study health centre laboratory and placed in an individual zippered plastic bag with a humidity indicator and 2–3 small silica gels. At APHI, approximately 20 DBS samples were stored within a larger zippered bag with silica gel pillows, humidity indicators and stored at −80°C.

##### Volumetric Absorptive Microsamples (VAMS)

Whole blood samples were collected using a volumetric absorptive microsampling (VAMS) device, MitraTM by Neoteryx (Torrance, CA, USA) from women while they were providing blood for routine laboratory testing by collecting additional drops, directly after collecting DBS samples (described previously). A total of 40 µL (4×10 µL) of blood was collected from the women at each timepoint by lightly touching the blood sample with the Mitra tip until it absorbed the required volume. In the absence of routine ANC phlebotomy in trimesters 2 and 3, whole blood was collected by the finger stick technique, with the Mitra tips hovering above the finger (without direct contact) until the tip turned fully red. Samples were air-dried either in their clamshell or over an empty 96-well collection plate for a minimum of 1 hour (max 3 hours). After drying, stored in Mitra autoracks (96-Sampler, item number: 108, Neoteryx, Torrance, CA, USA), wrapped in aluminium foil, placed in zippered bags with desiccant and transported to the APHI where they were transferred to a separate cryovial and stored at −80°C.

### Maternal stool

Participants were instructed by the health centre laboratory techs and study nurses on how to collect stool samples. Women were instructed to urinate into the toilet before collecting stool in the study-provided container while avoiding urine, soil, detergent, fragrance or water contaminating the sample. The laboratory tech evaluated the stool sample, completed the Bristol Stool Chart and measured the pH using nitrazine pH paper. Samples were then homogenised by using a plastic spoon and stirring the sample. Stool samples were aliquoted for Genotek analysis using an OMNIgene. GUT collection kit for TaqMan analysis was collected using a DNA/RNA shield tube. All stool samples were refrigerated at the local health centre after collection and transported to APHI. At APHI, Genotek samples were aliquoted into two cryovials and were stored at −80°C. TaqMan samples were first stored in the DNA/RNA shield tube, and additional stool was aliquoted into three cryovials and stored at −80°C.

### Infant blood

#### Umbilical cord and infant dried blood spots (DBS)

DBS samples were collected from the umbilical cord after delivery and from infants at 1–3 months. After delivery of the infant and placenta, the umbilical cord was double-clamped near the placenta and baby, cut and wiped with clean and dry gauze to remove maternal blood and contaminants. Umbilical cord blood was then drawn using an 18-gauge needle mounted on a 10 mL syringe with a luer tip. Four separate blood spots were then carefully dispensed onto a Whatman card. For infants, whole blood was collected by the heel stick technique. Samples were air-dried, transported and stored using the same procedures as maternal DBS samples.

### Infant stool

Mothers were instructed to wipe down the infant’s groin and public area with wipes provided by the study. Without applying any lotions or ointments, mothers lay the infant on the diaper or a cloth and stimulated the anal region using a wet cotton bud. Once the infant had a bowel movement, mothers collected the stool sample following the same instructions as their own samples (described earlier). Samples were processed, transported and stored using the same procedures as maternal stool samples.

A copy of the samples was shipped from Ethiopia to Boston, MA in the USA on dry ice and with temperature monitors for temporary storage and testing/analysis as previously described. Any samples with a single copy were retained in Ethiopia in compliance with Ethiopian regulatory requirements.

### Planned laboratory analyses

We intend to approach the analyses of our collected biospecimens using a coordinated multiomics approach to characterise the metabolome and microbiome of maternal and infant whole blood, serum and stool during pregnancy and in the postnatal period.^17^ Certain analyses will be coordinated with other prenatal BEP supplementation trials. Additionally, we will conduct analyses of certain biospecimens for micronutrient concentrations and inflammation biomarkers. Data from maternal urine and vaginal swabs will also provide insights into biological changes within women during pregnancy and breastfeeding. A comprehensive table of planned analyses is presented in table 3.

**Table 3 T3:** Summary of analyses to be performed on biospecimens

Biospecimen	Collection device	Planned testing	Analytic technique	Testing laboratory
*Maternal samples*				
Maternal whole blood	Whatman Card (DBS)	Thyroid function (TSH, T4, T3, TG) andleucocyte telomere length	ELISAs (eg, DBS-Tg assay) qPCR	Human Nutrition Lab, Zurich, SwitzerlandDrury Lab at Boston Children’s Hospital, Boston, MA, USA
Maternal whole blood	VAMS	Metabolomics	rLC-MS	Sapient Bioanalytics, San Diego, CA, USA
Maternal serum	EDTA tube	Ferritin, Soluble transferrin receptor (sTfR), total body iron, Hepcidin	ELISAs	TBD
Maternal stool	Genotek: OMNIgene.GUT	Microbiome profiling	Shotgun metagenomics	University of Wisconsin-Madison, WI, USA
Maternal stool	TaqMan: DNA/RNA shield tube	Enteropathogen profiling	qPCR	University of Virginia, VA, USA
Maternal urine	Poly tube	TSH, Tg, fT4, CRP, AGP, IL-6, IL-6R and iodine concentrations	ELISAs	Ethiopia Public Health Institute, Addis Ababa, Ethiopia
Maternal vaginal swab	Swab	Microbiome profiling	Shotgun metagenomics	TBD
*Cord/infant samples*				
Umbilical cord blood spot	Whatman card (DBS)	Metabolomics CRP, AGP, IL-6, IL-6R, TSH, Tg, fT4,	rLC-MS	Sapient Bioanalytics, San Diego, CA, USATBD
Infant blood	Whatman card (DBS)	Metabolomics andleucocyte telomere length	rLC-MS qPCR	Sapient Bioanalytics, San Diego, CA, USA [name] Laboratory at Boston Children’s Hospital, Boston, MA, USA
Infant stool	Genotek: OMNIgene.GUT	Microbiome profiling	Shotgun metagenomics	University of Wisconsin-Madison, WI, USA
Infant stool	TaqMan: DNA/RNA shield tube	Enteropathogen profiling	qPCR	University of Virginia, VA, USA

AGP, α1-acid glycoprotein; CRP, C-reactive protein; DBS, dried blood spot; EDTA, ethylenediaminetetraacetic acid; ELISA, enzyme-linked immunosorbent assay; qPCR, Quantitative Polymerase Chain Reaction; rLC-MS, rapid liquid chromatography–mass spectrometry; TBD, to be decided; VAMS, volumetric absorptive microsampling.

#### Inflammation

Maternal diet and infections during pregnancy both may influence inflammatory processes and impact the development and growth of the fetus and infant.^20 21^ Using infant and maternal DBS, we will examine the effects of the ENAT interventions on maternal and newborn inflammation biomarkers including C-reactive protein (CRP), α1-acid glycoprotein (AGP), interleukin-6 and 6R (IL-6 and IL-6R) and investigate the association of maternal and newborn inflammation on long-term neurodevelopment in infants.

